Clinical features	Impact of a multidisciplinary, personalized treatment plan including mobile palliative care (as needed) on the baseline to 6-, 12- and 18-months progression of motor, non-motor symptoms and time to clinical milestones of prospectively recruited MSA individuals, compared to sex-, age- (± 5 years), and disease duration- (± 12 months) matched MSA individuals from the historical EMSA-SG cohort^a^	- Baseline to 6-, 12- and 18-months change in motor and non-motor scales (total and subscores, including video-based, rater-blinded assessment of the UMSARS motor subscore and Hoehn & Yahr stage) - Time to clinical milestones (i.e. falls at least once a day, feeding by nasogastric tube or gastrostomy, unintelligible speech, indwelling catheter, wheelchair dependency)
	Baseline to 18-months therapeutic needs of individuals with early versus advanced^b^ MSA	- Medical and neuro-rehabilitation interventional needs over the 18-months study period (see MeDeMSA Operational Protocol in Supplementary Material 1)
	To compare the number of medical complications in individuals with early versus advanced^b^ MSA over the 18-months study period	- Number of medical complications (i.e., falls with or w/o injuries, urinary tract infections, choking, aspiration pneumonia, hospitalizations, death and others) over the 18-months study period
Psychological aspects	To compare the individual healthcare preferences at baseline and after 12 months in individuals with early versus advanced^b^ MSA	- Baseline and 12-months semi-structured online interview - Baseline to 12-months APIS change
	To compare the baseline to 18-months psychological counselling needs in individuals with early versus advanced^b^ MSA	- Psychological counselling needs of individuals with MSA over the 18-months study period (see modular intervention system in the MeDeMSA Operational Protocol, Supplementary Material 1)
	To compare the month 1, 7, 13, and final individual satisfaction with the personalized treatment plan in individuals with early versus advanced^b^ MSA	- Month 1 to 7, 13 and 18 SAPS change referred to the overall individualized treatment plan
Palliative care	To assess the feasibility and barriers to mobile palliative care in individuals with advanced^b^ MSA	- Structured documentation of the palliative intervention - Individual satisfaction with single mobile palliative interventions (IPOS)

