	To assess whether monthly multidisciplinary telemedicine visits in addition to a multidisciplinary, personalized treatment plan including mobile palliative care - Attenuate the baseline to 6-, 12- and 18-months QoL worsening - Attenuate the progression of motor and non-motor MSA symptoms, including time to clinical milestones in prospectively recruited MSA individuals compared to sex-, age- (± 5 years), and disease duration-(± 12 months) matched MSA individuals from the historical EMSA-SG cohort^a^ and to prospectively recruited MSA individuals receiving in-person visits and mobile palliative care (as needed) only	- Baseline to 6- and 12-months EQ-5D-5L score change - Baseline to 6-, 12- and 18-months changes in the MSA-QoL total score and subscores - Baseline to 6-, 12- and 18-months change in motor and non-motor scales (total and subscores, including video-based, rater-blinded assessment of the UMSARS motor subscore and Hoehn & Yahr stage) - Time to clinical milestones (i.e., falls at least once a day, feeding by nasogastric tube or gastrostomy, unintelligible speech, indwelling catheter, wheelchair dependency)
	To assess whether monthly multidisciplinary telemedicine visits in addition to a multidisciplinary, personalized treatment plan including mobile palliative care - Reduce the number of medical complications - Reduce the caregiver burden - Provide an advantage in terms of benefit-harm and cost-effectiveness tradeoffs - Increase the individual satisfaction with the personalized treatment plan over the 18-months study period in prospectively recruited MSA individuals compared to prospectively recruited MSA individuals receiving in-person visits and mobile palliative care (as needed) only	- Number of medical complications (i.e., falls with or w/o injuries, urinary tract infections, choking, aspiration pneumonia, hospitalizations, death and others) over the 18-months study period - Baseline to 6-, 12- and 18-months change in the EQ-5D-5L score of informal caregivers of prospectively recruited MSA individuals - Baseline to 6-, 12- and 18-months change in PQoL Carers score and other caregiver-burden indicators in informal caregivers of prospectively recruited MSA individuals - Baseline and 12-months semi-structured online interview - Single-intervention and cumulative healthcare costs over the 18-months study period - Month 1 to 7, 13 and 18 SAPS change

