## Methods

### Study design

This 18-month, monocentric, open-label study evaluates the impact of multidisciplinary, personalized best medical care, including mobile palliative and telemedicine support on the EQ-5D-5L score change of prospectively recruited MSA individuals compared to a sex-, age- and disease-duration matched historical European MSA cohort that received standard care [EMSA-SG cohort, (Wenning et al. 2013)], and whose data is stored at the Medical University of Innsbruck. The EMSA-SG cohort included individuals with MSA from ten countries, who underwent in-person assessments every six months over a 24-month period, showed largely comparable clinical-demographic characteristics across countries, but did not regularly receive treatment for MSA non-motor symptoms, neurorehabilitation, psychological counselling or palliative care offer (Kollensperger et al. 2010).

The study also assesses the participants'motor progression over 18 months using the Unified MSA Rating Scale (UMSARS) Part II through blinded video evaluations. Their progression is then compared to the motor progression curves of matched individuals from the EMSA-SG cohort.

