An overview of the study design is provided in Fig. 1, and the detailed MeDeMSA Care Visit Plan is reported in Table 2. After providing written consent, participants complete a home bladder and blood pressure (BP) diary for up to 72 h prior to the baseline visit, as well as a falls protocol referring to the month before the visit. During the baseline visit, participants undergo an in-person multidisciplinary assessment with the MeDeMSA Care study team. Following recommendations for PD settings (Bloem et al. 2021), the MeDeMSA Care team is composed of medical, neurorehabilitation, psychology, and palliative healthcare professionals with expertise in MSA care and is designed to meet the care needs that individuals with MSA may develop over the disease course. Baseline assessments include clinical, psychological, and neuro-rehabilitation evaluations, along with an online semi-structured interview on the individual healthcare preferences by the MeDeMSA team in Graz via a telemedicine platform currently used in the Tirol Kliniken [Computer-based Health Evaluation System, CHES, (Holzner et al. 2012)]. Additional tests, such as cardiovascular autonomic, sleep, urodynamic, or swallowing studies, are scheduled as needed during or shortly after the baseline visit. If not performed in the six months prior to the baseline visit, blood tests are conducted to check for undetected comorbidities (i.e., liver or renal failure) that could affect MSA medication dosages or require specific treatment (i.e., anemia, iron or vitamin deficiency). Following the baseline assessments, an individualized treatment plan is prepared using the MeDeMSA Care Operational Protocol (see Supplementary Material 1), which includes pharmacological and non-pharmacological measures, mobile palliative care for wheelchair-bound individuals, and guidance for self-practiced physiotherapy, occupational therapy, and speech therapy exercises (see Supplementary Materials 2, 3 and 4). The MeDeMSA Care Operational Protocol was developed by the MeDeMSA Care multidisciplinary study team based on available guidelines, consensus recommendations, scientific evidence and principles of good clinical practice. The protocol follows a “screen > diagnose > treat  with first-, second-, and third-line options” structure, designed to minimize the burden on recruited individuals and optimize healthcare resource allocation. Additionally, the treatment strategies are tailored to accommodate individual preferences, including the choice between pharmacological and non-pharmacological treatments, as well as among different types of pharmacological options or between tight symptoms’ control versus simplified medication schedules.

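### Video-rated UMSARS-II progression is compared with EMSA-SG curves that appear to come from in-person rating, so part of any slope difference could be rating mode, and rater blinding cannot rule this out

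*Protocol article*

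**What the plan says.** The Study design section of the protocol article describes the trial so: "This 18-month, monocentric, open-label study evaluates the impact of multidisciplinary, personalized best medical care". It assesses "motor progression over 18 months using the Unified MSA Rating Scale (UMSARS) Part II through blinded video evaluations". The next sentence fixes the comparator: "Their progression is then compared to the motor progression curves of matched individuals from the EMSA-SG cohort". The same section says of the EMSA-SG patients that they "underwent in-person assessments every six months over a 24-month period". It mentions no video recording or blinded re-rating of that cohort.

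Table 1 places the outcome among the secondary ones, as change in motor and non-motor scales: "total and subscores, including video-based, rater-blinded assessment of the UMSARS motor subscore and Hoehn & Yahr stage". It uses the same outcome for the telemedicine objective, where the comparators are EMSA-SG and, by randomisation, the arm described as "to prospectively recruited MSA individuals receiving in-person visits and mobile palliative care (as needed) only".

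The Data analysis section names repeated-measures ANOVA or linear mixed models for motor scores against matched EMSA-SG patients. It gives no term for rating mode and no bridging step. The Study design section lets patients who cannot travel complete on-site assessments online. Potential study limitations adds that patients outside the telemedicine arm may move to telemedicine follow-up, and names retention bias against EMSA-SG, but not rating mode.

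**The concern.** Scoring from a recording and scoring at the bedside need not be equally sensitive to change on the same scale. If one cohort is scored by video and the other in person, the cohort effect in the model contains both the programme and the mode. Matching on age, sex and disease duration cannot separate them, because the mode difference is complete between cohorts.

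The description of the rating as blinded could also give this comparison more credit than it earns. Blinding within the recruited cohort can conceal the visit and the telemedicine arm. With no EMSA-SG recordings mentioned, it cannot conceal which of the two cohorts a patient belongs to. At stake is the claim that the programme slows motor progression relative to historical standard care.

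**Working it through.** **No figure to reproduce.** The article gives no effect size, SD or power for UMSARS-II. The check is a reading of the text followed by an illustration on stated assumptions.

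**1. The two sides of the comparison**

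| | MeDeMSA cohort | EMSA-SG cohort |
|---|---|---|
| Motor rating | Blinded video (Study design; Table 1) | In-person assessments; scoring of UMSARS-II not described further |
| Visits | Baseline, 6, 12, 18 months, with an online option if travel is impossible | Every six months over 24 months |
| What blinding could hide | Visit order, telemedicine arm | No blinded rating mentioned |

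**2. What kind of mode difference biases a slope.** Let Y0 and Y18 be the scores that in-person rating would give.

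- Constant offset b at every visit: (Y18 + b) − (Y0 + b) = Y18 − Y0. No bias.
- Video registers a fraction f of in-person change: observed change = f × (Y18 − Y0). Apparent slowing = 1 − f. For f = 0.95 this is 5%, for f = 0.80 it is 20%. If f exceeds 1, the same size of error appears as faster progression. The article gives no reason to expect one direction over the other.
- A share p of patients is rated in a different mode at month 18 than at baseline, with offset b between the modes: bias in mean change = p × b. Here the offset does not cancel. The patients affected would be those too disabled to travel.

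**3. What blinding can reach.** The article states: "Following the baseline assessments, an individualized treatment plan is prepared using the MeDeMSA Care Operational Protocol". A baseline video therefore precedes the study treatment plan. If raters cannot tell baseline from month 18, their expectations can hardly steepen or flatten the MeDeMSA slope. This protection is real, but it leaves f and p × b unchanged. The article does not say what the raters are blinded to.

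**4. Illustration of consequence.** Assumptions: no true programme effect; 41 patients per group (46 × 0.9 = 41.4, one matched control each, matching ignored); normal approximation; two-sided 5% test; true mean 18-month change D of 0.5, 1.0 or 1.5 SDs of change. The spurious difference is s = (1 − f) × D, its standard error is √(2/41) = 0.221 SD, and the rejection rate is Φ(s/0.221 − 1.96) + Φ(−s/0.221 − 1.96).

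| f | D = 0.5 | D = 1.0 | D = 1.5 |
|---|---|---|---|
| 0.9 | s = 0.05, 5.6% | s = 0.10, 7.4% | s = 0.15, 10.4% |
| 0.8 | s = 0.10, 7.4% | s = 0.20, 14.8% | s = 0.30, 27.4% |
| 0.7 | s = 0.15, 10.4% | s = 0.30, 27.4% | s = 0.45, 53.1% |

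Worked cell, f = 0.9 and D = 1.0: s/0.221 = 0.453; Φ(−1.507) + Φ(−2.413) = 0.066 + 0.008 = 0.074. The same rates apply for f above 1 by the same margin, with the sign reversed. The result runs from negligible to serious, and nothing stated in the article would show which applies.

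**The case against.** Four points on the other side carry weight.

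- The EMSA-SG scoring mode is an inference. The article calls the assessments in-person, but MeDeMSA visits are in-person too, and it does not say how UMSARS-II was scored historically. This stands: the mismatch is very likely, not stated.
- Table 1 lists the video score as one item included among the motor scales, and the Data analysis section does not confine motor scores to video. In-person UMSARS-II may already be collected and compared. This stands and makes the fix feasible. Even so, Study design names the video score for the EMSA-SG comparison.
- Rating order and agreement statistics are commonly left to an analysis plan. Granted, and their absence is not the point. The point is that the article itself pairs a video score with an in-person comparator.
- Replacing the blinded score by the investigators' score would exchange a possible mode effect for unblinded rating in an open-label study. This also stands, so replacement is not recommended.

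A reader might go further and infer that blinding is worthless here because every video shows a treated patient. The documents do not support that. Baseline precedes the treatment plan, the outcome is change, and concealing visit order would limit expectation bias in the slope. Nor does the article claim that its blinding masks cohort membership.

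**Conclusion.** The concern holds in a limited form. As far as the article shows, rating mode coincides with cohort in the EMSA-SG motor comparison, so part of a difference in slope could be due to mode, in either direction. This requires that mode alters sensitivity to change, or that mode switches during follow-up; a constant offset does no harm. Blinding helps within the MeDeMSA slope if it covers visit order, and serves the randomised telemedicine comparison, but it does not extend to prospective versus historical.

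The size cannot be calculated from the article. The 5 to 20% apparent slowing and the rejection rates above rest on assumed values of f and D, not on evidence that video rating misses change. The outcome is secondary, and the primary EQ-5D comparison is not affected. The analysis should be amended, but the design need not change.

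**What to change.** 1. State what the video raters are blinded to. Have the recordings rated in random visit order, and keep this score for the randomised telemedicine comparison.
2. For the EMSA-SG comparison, report the in-person UMSARS-II change, labelled unblinded, beside the video-based change.
3. Report paired agreement between the two scores in change from baseline, in patients who have both. Since one score is blinded and the other is not, a disagreement signals a measurement problem without showing that mode alone caused it.
4. Mark the visits completed remotely, so that a switch of mode can be seen.
5. Interpret slower motor progression as a programme effect only if both scores agree, and add rating mode to the stated limitations.

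The cost is a little more analysis and an in-person comparison that is openly unblinded. The fix requires that in-person UMSARS-II is recorded at the on-site visits. The Fig. 1 legend expands UMSARS among its abbreviations but does not settle how it is scored. With 23 of the planned 46 patients recruited at the March 2025 revision, paired scores could still be secured for the patients yet to enter.

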
**Fig. 1 Fig1:**
[figure not shown]
MeDeMSA Care study design. * In the event that the enrolled subjects are for legitimate reasons unable to travel to hospital, they will be offered the opportunity to complete the scheduled on-site assessments of months 6, 12, and 18 using the CHES online platform. *10MWT* 10 m walking test; *24-ABPM* 24-h ambulatory blood pressure monitoring; *ACP* advance care planning; *APIS* autonomy preference index scale; *BBS* berg balance scale; *BBT* box and blocks test; *BMI* body mass index; *BP* blood pressure; *CAFT* Cardiovascular autonomic function tests; *CHES* computer-based health evaluation system; *COMPASS* composite autonomic symptom score; *EMSA- SG* European Multiple System Atrophy-Study Group; *EQ-5D-5L* European Quality of Life- 5 Dimensions- 5 Levels; *EQ-VAS* European quality of life- visual analogue scale; *FAC* functional ambulation categories; *FDA-2* Frenchay Dysarthria Assessment; *FEES* fiberoptic endoscopic evaluation of swallowing; *HADS* hospital anxiety and depression scale; *H&Y* Hoehn and Yahr Scale; *Ibk-RBD-5Q* Innsbruck REM sleep behavior inventory- 5 questions; *ISI* insomnia severity index; Laryngeal EMG laryngeal electromyography; *MDT-PD*: Munich Dysphagia Test- Parkinson Disease; *MMSE* mini mental state examination; *MSA- QoL* multiple system atrophy- quality of life; *MUCSS* Munich- Copenhagen Swallowing Screen; *OSA-DLS* occupational self-assessment- daily living scale; NHPT nine hole peg test; *PEG* percutaneous endoscopic gastrostomy; *QoL* quality of life; *RBD* REM sleep Behavior Disorder; *SARA* scale of the assessment and rating of ataxia; *TCT* trunk control test; *TUG* timed up and go test; UMSARS: unified multiple system atrophy rating scale

**Table 2 Tab2:**
[figure not shown]
MeDeMSA Care Patient Visit Plan

During follow-up in-person visits at 6-, 12-, and 18-months, the therapeutic needs are reassessed and the treatment plan is adapted as required. If subjects cannot travel to the center, they are offered the possibility to complete the scheduled on-site assessments via the CHES online platform. At month-12, the semi-structured interview is repeated to evaluate changes in healthcare preferences due to disease progression. Follow-up calls are scheduled one month after each in-person visit (at months 1, 7, and 13) to verify treatment compliance and address barriers. Short Assessment of Patient Satisfaction (SAPS) surveys are administered online at months 1, 7, 13, and 18 to evaluate the overall individual satisfaction with the treatment plan. In case additional in-person visits are scheduled, the reason for such visits and eventual therapeutic adaptations are documented.

Upon completion of the baseline assessment, 23 patients are block-wise randomized to additionally receive monthly and on-demand telemedicine visits for neurological, psychological, and neurorehabilitation support via CHES. If the individuals randomized to receive additional telemedicine visits own a tablet or computer with a ≥ 10-inch display, they may use it to enhance digital comfort. Otherwise, a CE-certified tablet (e.g., SAMSUNG Tab A7 T505 LTE 32 GB) is provided. The MeDeMSA Care team members are asked to rate telemedicine feasibility and potential barriers beforehand. After each telemedicine visit, healthcare providers give feedback on how the visit was conducted, document any challenges encountered, and note the adopted strategies to solve them. Brief patient satisfaction surveys follow telemedicine and mobile palliative care interventions: these include a 0–10 rating scale for the overall satisfaction with the intervention and open-ended questions about its advantages and disadvantages. The MeDeMSA Care team holds regular meetings every six to eight weeks to review changes in the care needs of recruited individuals with MSA and coordinate additional support as required.

Informal caregivers of the recruited individuals with MSA are invited to participate in an 18-month observational study, with QoL and caregiver burden assessed at baseline, 6-, 12-, and 18-months using a semi-structured interview and standardized questionnaires, including the EQ-5D-5L and PQoL Carers (Carers Quality of Life Questionnaire for Parkinsonism) (Pillas, Selai et al. 2016). The caregiver visit plan is reported in Table 3.

**Table 3 Tab3:**
[figure not shown]
MeDeMSA Care Caregiver Visit Plan

### Population

We plan to recruit 46 individuals, who fulfill all the inclusion criteria listed below:i.Age ≥ 30 years at the time of consent;ii.Diagnosed with clinically probable OR clinically established MSA according to the current criteria of the International Parkinson Disease and Movement Disorder Society (Wenning et al. 2022);iii.Life-expectancy of at least 24 months as assessed by the investigator at the time of consent;iv.Understands and agrees to comply with the study procedures and provides written informed consent (Note: a legal representative may NOT provide consent on behalf of the subject);v.Signed and dated informed consent document;vi.Fluency in German;vii.If unable to walk or stand without assistance/support at the time of consent, the participant must live in Tyrol or in another Austrian region with available mobile palliative care.

Candidates are excluded from the study if they meet any of the following conditions:i.Participation in an interventional clinical study at screening and throughout the study that would interfere with the MeDeMSA Care personalized treatment plan or would not permit telemedicine or mobile palliative care;ii.Charlson Comorbidity Index > 4 at the time of consent;iii.Other major underlying medical conditions that may confound interpretation of study results as assessed by the investigator.

We further plan to recruit up to 46 informal caregivers of individuals with MSA participating in the MeDeMSA Care trial, provided they meet the following inclusion criteria:i.Informal caregiver (i.e., a person not receiving payment for caregiving, except for care allowances and tax return schemes available in Austria) of an individual with MSA recruited in the present study;ii.Life-expectancy of at least 24 months, as assessed by the investigator at the time of consent;iii.Aged 18 or older at the time of consent;iv.Understands and agrees to provide information as outlined in the study protocol and to engage in semi-structured online interviews;v.Provides signed and dated written informed consent;vi.Full legal capacity;vii.Fluency in German.

Screening failures, i.e., patients who do not meet eligibility criteria at the time of screening, may be eligible for rescreening at a later time point. Rescreening is acceptable, for example, if individuals in the meantime conclude their participation in other interventional trials or if individuals previously not willing to engage in palliative care or telemedicine interventions change their opinion.

